## Abstract

**Introduction:**

The prevalence of type 2 diabetes (T2D) is 17% higher in rural dwellers compared to their urban counterparts, and it increases with age, with an estimated 25% of older adults (≥ 65 years) diagnosed. Appropriate self-care is necessary for optimal clinical outcomes. Overall, T2D self-care is consistently poor among the general population but is even worse in rural-dwellers and older adults. In rural Kentucky, up to 23% of adults in Appalachian communities have been diagnosed with T2D and, of those, 26.8% are older adults. To attain optimal clinical outcomes, social environmental factors, including social support, are vital when promoting T2D self-care. Specifically, peer support has shown to be efficacious in improving T2D self-care behaviors and clinical and psychosocial outcomes related to T2D; however, literature also suggests self-selected social support can be obstructive when engaging in healthful activities. Currently available evidence-based interventions (EBIs) using peer support have not been used to prioritize older adults, especially those living in rural communities.

**Method:**

To address this gap, we conducted formative research with stakeholders, and collaboratively identified an acceptable and feasible peer support EBI—peer health coaching (PHC)—that has resulted in improved clinical and psychosocial T2D-related outcomes among participants who did not reside in rural communities nor were ≥65 years. The goal of the proposed study is to use a 2x2 factorial design to test the adapted PHC components and determine their preliminary effectiveness to promote self-care behaviors and improve glycemic control among older adults living in Appalachian Kentucky. Testing the PHC components of the peer support intervention will be instrumental in promoting care for older adults in Appalachia, as it will allow for a larger scale intervention, which if effective, could be disseminated to community partners in Appalachia.

**Trial registration:**

This study was registered at www.clinicaltrials.gov (NCT06003634) in August 2023.

## Introduction

According to the Administration for Community Living [1], 16% (54.1 million) of the United States population is comprised of people aged ≥ 65 years, a percentage poised to rise to 21.6% (80.8 million) by 2040. In Kentucky, older adults account for an estimated 19% of the population, reflective of a 32% increase between 2009 and 2019. The rising number of older adults coincides with increased prevalence of chronic illness, including T2D. At present, an estimated 29% of older adults (≥ 65 years) have diagnosed or undiagnosed T2D [1]. Moreover, older adults living with T2D also have two times the annual healthcare expenditures as their younger counterparts—$13,239 versus $6,675, respectively [1].

Appropriate self-care behaviors are necessary for optimal clinical outcomes in T2D [2–4], accounting for 90% of variance in glycemic control [5]. Older adults living with T2D have more difficulty adhering to self-care regimens, and social environmental factors account for up to 85% of their self-care nonadherence compared to younger adults living with T2D [4, 6–10]. Notable social environmental factors include self-efficacy, distress, and lack of social support [11–14]. Specifically, social support plays a significant role in older adults’ T2D self-care and is thus an important social environmental factor to target in people with T2D [15]. Older rural-dwelling adults diagnosed with chronic disease have worse social function and emotional well-being than older adults living in urban areas [16]. Although social support has been shown to have a significant, independent relationship with T2D self-care, the extent and type of social support that may be available in rural communities might either positively or negatively impact older rural-dwelling adults’ self-care. The type and quality of social support can either reinforce or mitigate structural and psychosocial health determinants—such as healthcare mistrust, cultural health beliefs, and access to healthcare—that can influence self-care behaviors and beliefs [17–22]. Nevertheless, there remains a body of literature that substantiates the influence of social support on T2D self-care [15, 23] as well as the disproportionate burden of T2D in older adults [24].

In addition, frequency of desired social contact is also important for older adults. Previous research shows that more frequent social contact can mitigate depressive symptoms, frailty, and cognitive decline [25–27]. Frequencies of contact ranging from daily or weekly to monthly are each associated with health and wellbeing in older adults [25–27]. When designing and administering social support interventions in older adults, ensuring the appropriate type of support and determining the necessary contact frequency are both important considerations to providing appropriate social support for T2D self-care.

This study focuses on peer support. Peer support, wherein a person receives “support from a person who has experiential knowledge of a specific behavior or stressors and similar characteristics,” provides a mechanism for creating a social network that augments existing social supports [28]. In a systematic review of 25 randomized trials assessing structured peer support interventions for individuals with T2D, there were significant differences in HbA1c, blood pressure, cholesterol, and symptoms of hypo- or hyperglycemia between peer support and other study arms [29], highlighting the utility of structured peer support as an effective means to improving health behaviors and outcomes in low income and minority groups [30–33]. Because rural Appalachia Kentucky is characterized by close knit communities, the use of structured social support interventions, such as peer support, to promote desired health behaviors might be both feasible and acceptable to community members.

The present paper describes the research protocol for a feasibility study entitled, *Older Adults Using Social Support to Improve Self-Care (OASIS)*: *Adaptation*, *Implementation and Feasibility of Peer Support for Older Adults with T2D in Appalachia*. The goal of OASIS is to test specific components of a peer support intervention, PHC, and determine components that are most effective at promoting self-care behaviors and improving glycemic control among older adults living in Appalachian Kentucky.

## Methods

### Study aims

This study is guided by the following two aims:

#### 1. Use a 2x2 factorial design to determine which EBI components are associated with improved T2D-related outcomes in older adults living in Appalachia Kentucky

The independent variables for the factorial design are (1) how the peer coach is selected (self-selected by participant vs matched) and (2) frequency of contact (once per week vs every 2 weeks). We will evaluate effectiveness of each group using hemoglobin A1c (HbA1c) as the primary outcome while also evaluating self-care activities and T2D-related psychosocial factors as secondary outcomes

#### 2. Evaluate the pragmatic implementability of the adapted EBI

Guided by the Practical, Robust Implementation and Sustainability Model (PRISM), a framework that incorporates RE-AIM dimensions (i.e., reach, effectiveness, adoption, implementation, and maintenance). Interviews will be conducted at three timepoints: (1) at beginning of implementation, (2) at implementation midpoint, and (3) upon conclusion. We will collect both qualitative and quantitative data to assess PRISM domains and give context to both anticipated and unanticipated EBI adaptations. We will use an iterative approach to RE-AIM to collaboratively monitor RE-AIM dimensions, guide any needed mid-course adjustments, and evaluate implementation outcomes. Finally, feasibility, appropriateness, and acceptability of the EBI will be assessed via a validated 12-item questionnaire.

### Data safety, monitoring and management

The co-principal investigators (PIs; [name] and [name]) will ensure that all research personnel have undergone Collaborative Institutional Training Initiative (CITI) training for conducting human subjects research and gaining access to study data. They will monitor the study to ensure that all potential risks to participants remain minimal. In addition, all research personnel will be provided with a standard operating procedure manual that outlines recruitment strategies; the informed consent process including study procedures, contact information for the University of Kentucky Office of Research Integrity as well as the principal investigator, study timeline, and an appendix of required data collection documents; and a copy of the most recent consent forms and institutional review board study approval letter. The co-PIs will also invite the Office of Research Integrity to conduct mock audits on data collection and de-identification, encryption of audio files, and informed consent documentation to ensure research participants are properly protected.

#### Confidentiality

All data will be de-identified and stored on a password-protected computer at the University of Kentucky, including health information. In order to track participation over time, we will use an enrollment log that includes participants’ study IDs but will only use study IDs (e.g., de-identify) when entering data into REDCap. Only authorized individuals will have access to study data. Data and electronic records will be kept for a minimum of six years post-study closure. All precautions will be taken to keep participants safe. To secure against a potential breach of confidentiality, all study files will be deidentified and kept on a password-protected secure server at the University of Kentucky.

If there is any suspicion that a subject does not want to continue participating in the study, they will be withdrawn from the study. If a subject indicates that their participation in the study is causing distress, one of the co-PIs will telephone the participant within 24 hours to see how he/she is managing and may suggest he/she contact his/her primary care provider. In the event the subject does not have a primary care provider, one of the co-PIs will offer the subject a list of appropriate referral sources if he/she wishes. In addition, to avoid future incidents, each case of possible distress will be reviewed with the co-PIs and appropriate members of the investigative team, including review of study materials and responses to distressed participants. This review will evaluate whether any aspect of the study need requires modification.

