#### Plans to promote retention and complete follow-up

If a participant chooses to leave the study early, data collected until that point will remain in the study database and may not be removed. The intervention will no longer be provided to participants who are removed from this study, and participants will not be compensated for any sessions completed after being removed.

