#### Protocol nonadherence and amendments

Participants will not be removed from the study for nonadherence to the study protocol or for missing data. Protocol amendments will be communicated to funding agencies, trial participants, IRB officials, and trial registries.

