#### Random assignment of peer participants to intervention condition

Participants will be consented, enrolled and randomized into one of four groups. During the consenting process, it will be explained that participants can withdraw at any time. Participant can be randomized into one of the following groups: (1) self-select mentor, once per week contact; (2) self-select mentor, every two weeks contact; (3) matched with mentor, once per week contact; or (4) matched with mentor, every two weeks contact. For participants who are randomized into a group where they are matched with a peer health coach, matching areas include similarity of life stage (e.g., age), county of residence, and duration of disease diagnosis. However, the primary matching area for this study will be county of residence. This decision was informed by key informants who highlighted that Appalachians’ sense of identity is closely linked with the county in which they reside and that there will be an additional level of trust and comfort (or lack thereof) based on where their peer resides. For participants who are randomized into the group where they are able to self-select their peer coach, they will be provided with profiles of eligible coaches. These profiles will include age, sex, marital status, where they reside (county and town), duration of diabetes diagnosis, current HbA1c, and hobbies. Peer participants will be able to rank their top three coaches. The study team will try to match participants with their preferred coach. However, once a coach has been assigned three peer participants, they will be removed from the pool of coaches to choose from.

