### Intervention for peer coaches and participants

During the intervention, peer coaches interact with the peer participant for six months, with the frequency of interactions based on whichever group the peer participant was randomly assigned to as previously described. It is also optional for the peer coach to accompany the participant to at least one clinic visit. Topics to be discussed include current and target clinical goals for HbA1C, cholesterol, blood pressure, self-care activities, managing stress, and the SMART objectives. Coach-peer interactions will be documented with the following information: date, type of encounter (phone, in-person), duration, and topics discussed. Coaches will attend a monthly meeting to reinforce diabetes knowledge and communication skills. This meeting will be an open discussion based on their experiences interfacing with participants. Zoom will be used for the monthly meetings. Peer participants will receive a link to a brief REDCap survey by email every two weeks. If internet access is limited, we will send a hardcopy to the participant with a self-addressed stamped envelope. This survey will assess the frequency and duration of calls, other interactions with their peer, and the specific content that was covered. These self-report assessments will be used to track the effectiveness of the intervention.

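### Any suspicion of unwillingness withdraws a participant from the whole study without confirmation, and no outcome collection after leaving is described, so primary HbA1c values are lost avoidably

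*Protocol article*

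**What the plan says.** Four places in the protocol article bear on leaving the study.

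- *Confidentiality*: "If there is any suspicion that a subject does not want to continue participating in the study, they will be withdrawn from the study". The text does not say whose suspicion counts, what raises it, or that anyone asks the participant. Directly afterwards, a participant who reports distress is to be telephoned by a co-principal investigator within 24 hours. No such call is described for suspected unwillingness.
- *Protocol nonadherence and amendments* sets this limit: "Participants will not be removed from the study for nonadherence to the study protocol or for missing data".
- *Plans to promote retention and complete follow-up* has this rule for early leavers: "If a participant chooses to leave the study early, data collected until that point will remain in the study database and may not be removed". On the coaching itself, the same section then says: "The intervention will no longer be provided to participants who are removed from this study". Despite its title, this section does not mention measuring outcomes after a participant leaves.
- *Random assignment of peer participants to intervention condition*: "During the consenting process, it will be explained that participants can withdraw at any time". Here withdrawal is the participant's own decision.

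On measurement, *Study measurements and outcomes* schedules participants' HbA1c and questionnaires at baseline, 6, 9 and 12 months. *Analytic plan for aim 1* makes HbA1c at the first post-intervention occasion the main outcome. It uses a linear mixed model that keeps participants with some occasions missing.

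**The concern.** The rule in *Confidentiality* is unconditional and its threshold is very low. It ends participation as a whole, and it can do so for someone who would have agreed to one more fingerstick at month 6. That value cannot be recovered in the analysis.

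The rule also sits uneasily with the promise not to remove people for nonadherence or missing data. A participant who goes quiet may look unwilling to one person and merely nonadherent to another. The first reading leads to removal and the second to retention, so who is followed up could depend on who makes the judgement.

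At stake are the precision of a study with 38 participants per factor level and, if those withdrawn differ in glycaemic control from those who stay, the validity of the 6-month contrast. The study exists to supply variability and effect estimates for a larger trial, so avoidable and possibly informative loss would carry over into that trial's planning.

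**Working it through.** **Inputs**

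- 19 per condition, 76 in total (*Sample size*), so 2 × 19 = 38 per level of each factor.
- Detectable f = 0.33 at 80% power, two-sided α = 0.05 (*Sample size*).
- Attrition is anticipated in *Sample size*, but no rate is given. Every loss rate below is therefore an assumption.
- "peer coaches interact with the peer participant for six months" (*Intervention for peer coaches and participants*), weekly or every two weeks. Taking six months as 26 weeks gives 26 or 13 scheduled contacts.

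**Step 1: the rules side by side**

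| Situation | Rule that applies | Result |
|---|---|---|
| Participant says they are leaving | *Random assignment*; *Plans to promote retention* | Leaves; earlier data kept |
| Misses contacts or surveys, no suspicion of unwillingness | *Protocol nonadherence* | Stays |
| Misses contacts or surveys, and someone suspects unwillingness | *Confidentiality* says withdraw; *Protocol nonadherence* says these lapses are not grounds | Not settled |

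The third row is the gap. The article does not say that missed contacts raise suspicion; that they might do so is an inference.

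**Step 2: HbA1c values available if measurement stops on withdrawal**

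| Withdrawn | Values available | Primary outcome |
|---|---|---|
| Before month 6 | Baseline | Lost |
| Between months 6 and 9 | Baseline, 6 | Kept |
| Between months 9 and 12 | Baseline, 6, 9 | Kept |

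The mixed model can retain someone with baseline only, but that person adds little to the 6-month contrast. The model is valid only if, given baseline and assigned condition, withdrawal is unrelated to the unseen 6-month value.

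**Step 3: the plan's own figure**

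Use the noncentral F with 1 numerator df, N − 4 denominator df and noncentrality f²N. At N = 76 the detectable f is 0.326 and power at f = 0.33 is 81.0%. The stated 0.33 is reproduced as a main-effect figure at the full sample. A 3-df comparison of four groups gives 0.389 and does not match.

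**Step 4: overall loss (assumed)**, counting withdrawn participants as contributing nothing at month 6

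| N analysed | Loss | Power at f = 0.33 | Detectable f |
|---|---|---|---|
| 76 | 0 | 81.0% | 0.326 |
| 72 | 4/76 = 5% | 78.8% | 0.335 |
| 68 | 8/76 = 11% | 76.4% | 0.345 |
| 60 | 16/76 = 21% | 71.0% | 0.368 |

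This counts all loss. How much of it the suspicion rule would cause is unknown.

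**Step 5: loss by contact frequency (assumed)**

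Suppose each scheduled contact independently carries a chance q of triggering withdrawal. Loss is then L = 1 − (1 − q)^k, with k = 26 (weekly) or 13 (every two weeks). For q = 1%: 1 − 0.99^26 = 0.230 and 1 − 0.99^13 = 0.122.

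Power uses the normal approximation with d = 2 × 0.33 = 0.66: Φ(0.66/√(1/n₁ + 1/n₂) − 1.96), which is 82.0% with no loss. If withdrawn participants differ from stayers by δ SD in HbA1c, the completers' contrast shifts by δ × (difference in loss).

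| q | Loss weekly | Loss two-weekly | Power | Shift, δ = 0.5 to 1 SD |
|---|---|---|---|---|
| 0.2% | 5.1% | 2.6% | 80.5% | 0.01–0.03 SD |
| 0.5% | 12.2% | 6.3% | 78.2% | 0.03–0.06 SD |
| 1% | 23.0% | 12.2% | 74.1% | 0.05–0.11 SD |
| 2% | 40.9% | 23.1% | 65.3% | 0.09–0.18 SD |

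If withdrawal does not depend on the number of contacts, loss is equal. At 10% in both levels, power is 77.9% and the shift is zero.

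**The case against.** The best defence is that the two sentences concern different things. One protects people who no longer wish to take part; the other reassures people who are merely nonadherent. Both can hold at once, and the second can be read as limiting the first. Placed beside the distress procedure, the suspicion rule reads naturally as a safeguard of voluntariness. This stands: a reader might infer a contradiction, but the text shows only that the rules are not reconciled.

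A reader might also infer that study staff would withdraw people because of missed calls. The article names neither staff nor any trigger.

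A third tempting reading is that the weekly conditions will lose more people. The scheduled contacts are with peer coaches, and nothing says that coach logs prompt withdrawal. The participant survey follows one schedule, with no difference by condition stated: "Peer participants will receive a link to a brief REDCap survey by email every two weeks". Sparser contact could equally cause more disengagement. The roughly two-to-one losses in Step 5 follow from the assumed per-contact hazard, so they illustrate a mechanism and do not estimate it.

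The retention section is a rule about keeping data and does not state that measurement ends. Nor does every withdrawn participant lose the primary outcome; those leaving after month 6 keep it.

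Finally, an article may leave procedures to a full protocol or to the operating manual that it mentions. That would excuse a missing detail. It does not excuse a rule that the article states in unconditional terms, with no confirmation step and with withdrawal from the study as its result.

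**Conclusion.** The concern holds in a limited form. The protocol fixes a withdrawal rule that needs no confirmation, applies to the whole study, and is not reconciled with the rule on nonadherence and missing data. Because no outcome collection after leaving is described, a participant withdrawn before month 6 would have only a baseline HbA1c. This assumes that measurement stops on withdrawal, which the article implies but does not say.

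The cost in precision is moderate and depends on a loss rate that the article does not give: about 5 percentage points of power if 8 of 76 are lost and about 10 if 16 are lost, from all causes together. The possible bias cannot be sized from the document. That disengaged participants have poorer glycaemic control is plausible but unsupported by any figure there.

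Differential loss by contact frequency is possible, with size and direction unknown, and the point does not depend on it. This should be changed because the loss is avoidable and the change is cheap; it does not invalidate the design.

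**What to change.** 1. Reconcile *Confidentiality*, *Plans to promote retention and complete follow-up* and *Protocol nonadherence and amendments*, so that one rule says what happens to a participant who appears disengaged.
2. Confirm suspected unwillingness with the participant before recording a withdrawal. The right to leave at any time is unchanged.
3. For data collection, separate the end of coaching from the end of outcome measurement. Continue to request the scheduled 6-, 9- and 12-month HbA1c and questionnaires unless the participant declines further data collection.
4. Record who initiated each withdrawal, the reason and the date, and report these by condition, so that any difference by contact frequency can be seen.

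The cost is protocol and consent wording, two or three extra fields on the withdrawal form, and a few follow-up calls. No visits are added. The calls should be worded so that someone reluctant to refuse openly can still decline easily.
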